### Sample Size Calculation

The yearly average number of completed RAI-HC assessments is ~20,000-30,000 in Alberta, ~34,000-39,000 in British Columbia, and ~10,000 in Manitoba [67]. About 50% of those assessed receive a reassessment within 12 months and another 10%-30% receive a reassessment after >15 months [68]. There are 89 publicly subsidized day programs in Alberta (~3300 spaces per day), 95 in British Columbia (~1500 spaces per day), and 70 in Manitoba (~1000 spaces per day) for a total of 254-day programs with 5800 spaces on any given day. Some day program users do not attend daily, but only 1 or a few days per week, so the number of unique attendees exceeds the number of spaces per day. This corresponds to >20,000 attendees per year (>200,000 within the study period), each with multiple assessments. Our study sample size will be large enough to detect small effects sizes. With Cox proportional hazards models, adjusted for covariates explaining an assumed 25% of effect variance (a=.05; power=0.8) [69], we require a total sample of 1327 participants to detect a hazard ratio for admissions to care homes of 0.6 (as can be expected based on a similar Canadian study [42]) in favor of day program attendees. Similarly, Kelly [43] was able to detect significantly fewer emergency department visits and hospital admissions per day among 812 day program attendees compared with 812 propensity score matched to nonattendees. Our expected sample size will be considerably larger than for those previous studies, allowing for complex statistical modeling.

### Data Sources

For each individual in our cohort, designated provincial health system analysts will link all records available within the study time frame from the following databases: (1) regional continuing care registries, documenting when an individual starts or stops receiving any community-based continuing care, including day programs, how these services change over time, and when an individual is admitted to a care home. (2) Population registries for each participant’s demographic data. (3) RAI-HC assessments [64], completed annually for people receiving long-term home care (60+ days), and to determine day program eligibility. The RAI-HC will provide data on older adults’ medical conditions, functional dependence, pain, cognitive impairment, mood, and behavioral problems. It also includes information on a person’s marital or partnership status, caregiver availability, whether that caregiver lives with the older adult, and caregiver distress. Additional caregiver characteristics are not included in the available provincial databases, posing a limitation to our quantitative analyses. However, a related prospective cohort study that we are conducting in Ontario will allow us to link comprehensive caregiver and older adult data, and we are currently conducting additional qualitative research that will illuminate how caregiver characteristics may affect day program use and outcomes. (4) Discharge abstract database (DAD) for information on all inpatient hospital stays, including diagnoses and length of stay. (5) National Ambulatory Care Report System (NACRS) for all emergency department visits and diagnoses. In British Columbia, we will use the physician payment file in addition, since NACRS is not collected in all emergency departments [70]. (6) Pharmaceutical information on outpatient prescription medications filled through a community pharmacy and covered by provincial drug formulary. (7) Care provider claims data for health service claims submitted for payment by health care providers (eg, general practitioners, nurse practitioners, geriatricians, geriatric psychiatrists, neurologists, therapists) to obtain information on general and specialist health services used by participants.

### Study Variables

#### Exposure

Our exposure will be different patterns of day program use or nonuse, based on information from the provincial continuing care registries, documenting the dates a person starts or stops attending a day program, days of attendance, and the duration of each visit. Day program use patterns will be determined, using LCAs (see *Statistical Analyses* section) [71]. We will categorize three continuous variables as low, low-moderate, high-moderate, or high use, using sample distribution quartiles: (1) time between first RAI-HC assessment and first attendance of a day program; (2) average number of hours of day program attendance (ie, total number of hours spent in a day program divided by the number of times attended); and (3) total number of days a person attended a day program. LCAs will also include a categorical variable, indicating whether a person consistently attended a day program or whether there were longer periods (several weeks) of nonattendance. Nonuse will be defined as no day program exposure at any time during a person’s continuing care trajectory.

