Explore patterns of day program use (eg, variations in time to first attendance, monthly hours of attendance, ongoing versus interrupted attendance, and total time of day program exposure), using latent class analyses (LCA), and compare the frequency of each latent use class between provinces and over time.Compare older adults’ demographic, social, and health characteristics (eg, age, sex, physical or cognitive disability, area-based deprivation indices, and caregiver availability or distress) by day program use or nonuse class, province, and time.Assess whether, compared with a propensity score–matched control group of nonattendees, day program attendees enter care homes at later points in time; use emergency, acute, or primary care less frequently; experience less cognitive and physical decline; have better mental health; and have less distressed caregivers. We will assess potential modification of these effects by day program use or nonuse class, age, sex, and social determinants of health (eg, area-based deprivation indices).

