### Statistical Analyses

#### Objective 1: Explore Patterns of Day Program Use

Using our day program cohort, we will conduct LCAs to determine the number of different day program use patterns, using the 4 variables described in the exposures section. LCAs are widely used to identify subgroups by clusters of characteristics (ie, parameters of day program use) [71]. In collaboration with our experts and guided by relevant literature, we will prespecify the expected number of classes. We will carry out LCAs separately in each province. We will run models with the prespecified number of classes, and with 1, 2, and 3 more and fewer classes than the number prespecified [71]. We will compare the fit between models, using bootstrap likelihood ratio tests [71], and select a final model that reflects the same number and types of classes in each province, balancing theoretical, conceptual, and statistical considerations. To assess temporal changes in the number of day program attendees within each use pattern, and differences between provinces, we will report and graphically plot the proportion (95% CI) of individuals within each latent class by quarter and province.

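### Objective 1 names monthly hours of attendance, but the latent class analysis uses mean visit length and has no rate per calendar time, so weekly frequency is confounded with length of enrolment

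*Protocol article*

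**What the plan says.** In the protocol article, the objectives at the end of the Introduction describe day program use by examples: "variations in time to first attendance, monthly hours of attendance, ongoing versus interrupted attendance, and total time of day program exposure".

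The Exposure section turns this into four inputs. Three are continuous and cut at sample quartiles:

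1. "time between first RAI-HC assessment and first attendance of a day program";
2. an hours variable, defined as "total number of hours spent in a day program divided by the number of times attended";
3. "total number of days a person attended a day program".

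The fourth is categorical: "whether a person consistently attended a day program or whether there were longer periods (several weeks) of nonattendance".

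The statistical section for objective 1 confirms that the latent class analysis is run "using the 4 variables described in the exposures section"; no other input is named. The resulting class, with nonuse as a further category, is an independent variable in the objective 2 models and in the time-to-event and GEE models of objective 3.

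**The concern.** The two lists correspond item by item except for hours. The Introduction speaks of hours per month; the Exposure section divides by visits, which gives the length of a typical visit. Someone who attends every weekday and someone who attends once a week have the same value if their visits are equally long.

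The plan itself treats frequency as a real source of variation. The Introduction says that days attended differ widely between users and jurisdictions. The sample size section says "Some day program users do not attend daily, but only 1 or a few days per week" and relies on this to argue that attendees outnumber spaces.

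At stake is what a use class means. If frequent and infrequent attendees share a class, the description of users by class (objective 2) and the class-specific effects (objective 3) average over people whose monthly attendance may be very different, and the pattern that objective 1 names is not measured directly.

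**Working it through.** The plan gives no figure that depends on this definition, so there is none to reproduce. The check computes the four stated inputs, and monthly hours, for constructed attendees.

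**Inputs.** The variable definitions come from the Exposure section. Assumptions: 6 hours per visit, equal time to first attendance, steady attendance, and 30.44 days per month. Steady weekly attendance has no gap of several weeks, so both attendees count as consistent.

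**Formulas.** Total days = days per week × weeks. Hours per visit = total hours / visits. Monthly hours = total hours / (days enrolled / 30.44).

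**Pair with unequal enrolment**

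- Attendee A: 5 × 8 = 40 days; 40 × 6 = 240 h; 240 / 40 = 6.0 h per visit; 240 / (56 / 30.44) = about 130 h per month.
- Attendee B: 1 × 40 = 40 days; 240 h; 6.0 h per visit; 240 / (280 / 30.44) = about 26 h per month.

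All four inputs agree, while monthly hours differ 5-fold. No choice of quartile cut points or number of classes can separate A from B. The same happens with 5 days a week for 20 weeks against 1 day a week for 100 weeks: both give 100 days and 6.0 h per visit, with 130.4 versus 26.1 h per month.

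**Pair with equal enrolment.** Over 52 weeks, 5 × 52 = 260 days against 1 × 52 = 52 days. Here total days does separate the two. It is therefore a partial proxy for frequency, confounded with duration.

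**Illustration of the overlap.** Assume attendance of 1, 2, 3 or 5 days a week in 35%, 35%, 20% and 10% of attendees, and log-normal enrolment, independent of frequency, with median 40 weeks and log-scale SD 0.9. Simulating 200,000 attendees gives, by quartile of total days:

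| Quartile | Once weekly | 5 days a week |
|---|---|---|
| Lowest | 64.5% | 1.2% |
| Second | 41.2% | 4.1% |
| Third | 24.9% | 9.6% |
| Highest | 9.8% | 25.0% |

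Total days tracks frequency, but every quartile holds both kinds of attendee. These percentages follow from the assumed mix and are not estimates for the three provinces.

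**With a rate added.** Days per month would be 40 / (56 / 30.44) = 21.7 for A and 40 / (280 / 30.44) = 4.3 for B, so the pair separates.

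**The case against.** Five points can be made for the plan.

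- *Intensity is not absent.* Hours per visit measures intensity within a visit, and total days rises with frequency when enrolment lengths are similar. This stands. A reader might infer that the inputs contain no attendance intensity, or that the classes can carry no information on frequency; the 260 versus 52 comparison shows otherwise.
- *The colliding pair is constructed.* Frequency and duration were set in exact inverse proportion. The article gives no joint distribution of the two, and the Introduction says that attendance often lasts months or years. So the extent of misclassification is unknown, and the 5-fold figure describes chosen pairs. However, the inputs enter as quartile categories, so two attendees need only fall in the same quartiles, not match exactly.
- *The Introduction's list is only illustrative.* It is given as examples, and the Exposure definition is explicit and workable. This softens the mismatch but does not remove it: the other three examples recur recognisably in the Exposure section, and only this one is replaced by a different quantity.
- *Visit length is a legitimate dimension.* The Introduction names time per day as varying, alongside number of days. This stands, and it argues against simply swapping visit length for monthly hours: monthly hours alone cannot tell two 4-hour visits a week from one 8-hour visit.
- *The main contrast is untouched.* This also stands. Nonuse is defined without the latent classes, and the propensity score models attendance versus nonattendance.

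**Conclusion.** The point holds in a limited form. The Introduction and the Exposure section define the hours dimension differently, and none of the four stated inputs separates weekly frequency from length of enrolment. Attendees whose monthly hours differ 5-fold can have identical inputs and so fall in the same class. That result needs only the stated definitions, equal visit length, equal time to first attendance and steady attendance. How often it would happen in the data cannot be derived from the article.

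The consequence is blurring of the class comparisons in objectives 2 and 3. Two stronger readings are not supported. One is that the matched comparison is compromised: the matching of attendees to nonattendees and the sample size calculation do not use the hours variable. The other is that a null or inconsistent class effect would be explained by this pooling: it would be one possible explanation, and nothing in the article shows that it would be the reason.

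Because the class is the exposure in the outcome models, and the same programs are to be run separately in three provinces, the definition is best settled before the class models are run.

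**What to change.** In the Exposure section, add a calendar-time rate as an input to the latent class analysis: hours or days attended per month between the start and stop dates, excluding the gaps that the interruption variable already captures, with a stated minimum denominator so that very short enrolments do not produce extreme rates. Categorise it by the same quartile rule. Keep visit length as an input or as a descriptor of the classes. If it stays an input, days per month is the cleaner rate, because hours per month is the product of days per month and visit length.

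Then align the wording of objective 1 in the Introduction, the Exposure section, and the objective 1 analysis text, which now refers to four variables.

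No new data are needed: the Exposure section says that the registries record start and stop dates, days attended and the duration of each visit. The cost is one more derived indicator in the shared program and a slightly larger latent class model.

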### Setting and Sample

Our study settings are community-based continuing care systems. Each province provides access to a range of publicly funded community-based continuing care services, including adult day programs [55-63]. Each provincial health system determines and enacts access criteria and provides services (directly or via contracted providers) [55-63]. Day program eligibility is assessed in each province, using comparable processes, criteria, and assessments (ie, the Resident Assessment Instrument—Home Care [RAI-HC], a standardized, valid, reliable assessment tool [64]) [60,65,66]. To be eligible, attendees need to have not only some care dependency but also the ability to cope to some extent with activities of daily living, ambulate or transfer with no or minimal assistance, be continent or independent in managing continence products, exhibit no or easily manageable responsive behaviors, and either be alone for extended periods or have a caregiver who requires respite. Our study cohort will include all individuals aged 65 years or older with an initial RAI-HC assessment completed between January 1, 2012, and December 31, 2021. We will follow everyone until they move into a care home, are lost to follow-up (eg, because of death, moving out of province, loss of public insurance eligibility), or until December 31, 2024 (the end of the period covered by our data). That will allow for a care trajectory of at least 3 years (for those with an initial RAI-HC assessment in December 2021), enabling us to assess the number and characteristics of individuals with different day program use patterns, and compare them with those who were never exposed to a day program.

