#### Objective 3: Assess Effects of Day Programs

To create a propensity score, we will run a logistic regression for each province with day program attendance or nonattendance as the dependent variable and adding matching covariates. We will use one-to-one matching (1 matched nonattendee for every attendee) [78]. We will use matching without replacement [85] and apply an optimal caliper matching algorithm [86]. As per best practice recommendations [87], we will use a caliper width of 0.2 of the SD of the propensity score’s logit. If this matching approach does not allow us to achieve a sufficient sample size, we will use propensity score quintiles for matching.

We will compare sample characteristics and study outcomes between attendees and nonattendees in every year and province, using bivariate statistical tests (eg, chi-square test or Fisher exact test for categorical variables, *t* tests, or ANOVAs for continuous variables, and their nonparametric equivalents if variables violate statistical assumptions). To assess the effect of day program exposure on time to care home admission, we will specify a multilevel time-to-event model with a health region–level random effect [88]. Health systems in each of the 3 provinces are divided into 5 health regions [89-91], and regional policies may cause clustering effects that our models must account for. Each model will include day program use or nonuse class as independent variable and will be adjusted for time-varying variables. These will include matching variables, if appropriate (ie, in case of group differences in matching variables over time or due to missing data) [80-82] and, if needed, additional covariates (eg, demographics, social determinants, medical or functional conditions, and non–day program community care). Covariates that differ between attendees and nonattendees with a *P* value of ≤.15 in the bivariate analyses will be considered for inclusion. We will add covariates stepwise, one-by-one, and remove those that cause collinearity issues or decrease model fit. As in objective 2, we will pool provincial effects statistically, using random-effects mixed regression models.

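### In objective 3, the use class that explains time to care home admission is built from attendance that admission itself cuts short, so class effects on admission mix any real effect with an artefact.

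*Protocol article*

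**What the plan says.** All references are to the protocol article.

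- **Exposure.** Use patterns come from an LCA with four indicators: time from first RAI-HC to first attendance, mean hours per visit, a third given as "3) total number of days a person attended a day program", and whether attendance was consistent or had gaps of several weeks. The first three are cut at quartiles: "We will categorize three continuous variables as low, low-moderate, high-moderate, or high use, using sample distribution quartiles". No window limits the total or the gaps. Nonuse means "no day program exposure at any time during a person’s continuing care trajectory".
- **Setting and Sample.** "We will follow everyone until they move into a care home, are lost to follow-up", or until December 31, 2024. Loss includes death. Entry runs from 2012 to 2021.
- **Study Outcomes.** Time to care home admission is counted from the first RAI-HC.
- **Objective 3.** "Each model will include day program use or nonuse class as independent variable and will be adjusted for time-varying variables". The term time-varying applies to the adjustment variables, not to the class.

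**The concern.** An exposure that predicts a time-to-event outcome should be settled before the time at risk begins, or be updated as that time passes. Here neither holds. Someone admitted four months after starting a day program cannot accumulate many days, however intensively they attend. Someone who stays at home for eight years can. The first tends towards a low-use class and the second towards a high-use class because of the outcome. The gap indicator has the same weakness, since long interruptions need long observation.

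Time to first attendance fails differently. It is known at the first visit, but with the clock starting at the first RAI-HC, a long wait can be recorded only for someone who was not admitted during it. That is immortal time.

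At stake is the central effect estimate of objective 3. An apparent delay in admission among heavy users could arise with no program effect at all.

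**Working it through.** **1. The plan's own figure.** The planning HR of 0.6 is used below as a yardstick. For its total of 1327, the two-sided Schoenfeld formula at 1:1 allocation gives (1.960 + 0.842)² / (0.25 × (ln 0.6)²) ≈ 120.3 events. Dividing by 1 − 0.25 for the covariates gives 160.4, and 160.4 / 1327 implies 12.1% admitted. The article states no event proportion, so 1327 can be neither confirmed nor refuted. The point does not depend on it.

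**2. Structure.** Days attended ≈ attendance rate × min(time from first attendance to exit, time to voluntary stopping). Exit is the earliest of admission, other loss and December 31, 2024. Admission time, the outcome, is therefore an argument of the exposure. Matching on index-date covariates does not remove this, because class is assigned from later attendance.

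**3. Size with total days alone, true HR 1.** The documents give none of the rates, so all are assumptions.

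- Setting A: admission 0.12 per year, death 0.15 per year, mean wait 6 months, about 78 attendance days per year with gamma variation, 40,000 people.
- Setting B: admission 0.08, 0.15 or 0.25 per year, death 0.08 per year, censoring at 3 to 13 years, half intending to attend, mean wait 1 year, 52 to 260 attendance days per year unrelated to prognosis, voluntary stopping 0.15 per year, 8 replicates of 12,000 people.

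Cox HR against nonuse, by quartile of total days:

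| Setting | Lowest | 2nd | 3rd | Highest |
|---|---|---|---|---|
| A, attendance until exit | 3.6 | 1.3 | 0.65 | 0.30 |
| A, 40% per year stop for unrelated reasons | 1.16 | 0.94 | 0.73 | 0.50 |
| B, clock from first RAI-HC | 1.25–1.33 | 0.83–0.88 | 0.58–0.62 | 0.36–0.38 |
| B, clock from first attendance | 2.13–2.52 | 1.29–1.38 | 0.87–0.89 | 0.50–0.51 |

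The last row shows that moving the clock alone does not repair the class comparison.

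**4. Size with an LCA on all four indicators.** Setting A rates, true HR 1, clock from first RAI-HC, hours per visit unrelated to outcome, gaps assumed at 0.3 per year. Classes run roughly from low to high use:

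| Stopping | Run | Class HRs against nonuse |
|---|---|---|
| None before exit | 4 classes | 1.90, 1.57, 0.70, 0.40 |
| None before exit | 4 classes | 1.63, 1.72, 0.48, 0.43 |
| None before exit | 4 classes | 1.85, 1.70, 0.79, 0.46 |
| None before exit | 3 classes | 1.35, 1.54, 0.47 |
| 40% per year | 4 classes | 0.99, 1.05, 0.71, 0.56 |
| 40% per year | 4 classes | 0.88, 1.00, 0.63, 0.54 |
| 40% per year | 4 classes | 1.03, 0.70, 0.65, 0.61 |
| 40% per year | 3 classes | 1.05, 0.80, 0.61 |

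The highest-use class lies between 0.40 and 0.61 in every run.

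**5. Overall comparison.** In Setting B, ever against never attending, timed from first RAI-HC, gives 0.65 to 0.71 with no effect. People who leave before they could start count as nonusers.

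**6. Does a remedy remove it?** In Setting B, classes fixed from first-year attendance with a 1-year landmark give 0.97 to 1.07. Attendance as a time-varying term (started or not) gives 0.99 to 1.00. The landmark runs compared attendees only with people who never intended to attend, so they test the class gradient but not the future-based definition of nonuse. The time-varying runs included everyone.

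**The case against.** The best defence is that the planned exposure is a four-indicator latent class, not a quartile of total days. Mean hours per visit hardly depends on length of follow-up, and time to first attendance is fixed at the first visit. Registries also record people who stop for other reasons, so an HR of 3.6, which needs everyone to attend until exit, is an extreme. This stands as far as size goes: the LCA runs are weaker, and with unrelated stopping the lowest class sits near 1. It does not remove the bias in the highest-use class.

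An unseen analysis plan might add detail. But the article itself fixes the indicator, the end of observation, the outcome and the class term, and a plan that carried these out as written would keep the bias.

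Several stronger readings are tempting but not supported:

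- *Class effects are nothing but reverse causation.* A real effect may exist; it cannot be separated from the artefact. Death and the end of data also cut the total short.
- *A steep dose-response with harmful low use is certain.* The LCA runs with unrelated stopping do not show it.
- *Intensity is never measured.* The objectives mention "monthly hours of attendance" only as an example, and the variable defined is "total number of hours spent in a day program divided by the number of times attended". Total days still separates frequent from rare attenders, although it mixes frequency with duration.
- *Class trends over calendar time reflect follow-up length.* Follow-up is planned so that "That will allow for a care trajectory of at least 3 years" for the last entrants, and it can reach about 13 years for the first. Yet the top-quartile share differed by entry year (30% against 10%) only when attendance lasted until exit, with no clear difference under unrelated stopping.
- *Matching leaves each class unbalanced.* This is a separate matter, and the model may adjust for matching variables where groups differ.

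**Conclusion.** The point holds for objective 3. As written, the fixed class in the time-to-admission model depends on the outcome through total days and gaps, and carries immortal time through time to first attendance. With no true effect, the highest-use class can show an HR of about 0.40 to 0.61, which is hard to tell from the 0.6 that the study hopes to find. The overall attendee comparison is not a safe fallback if it is timed from the first RAI-HC.

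The direction in the highest-use class was the same in every run. The size rests on assumed rates of admission, death, waiting, stopping and gaps, and on hours per visit being unrelated to outcome. That the total covers the whole trajectory is a reading of the text: no window is given, and both the word total and the definition of nonuse point that way. Descriptive use of the classes in objectives 1 and 2 is not undermined in the same way.

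**What to change.** For objective 3 only:

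1. Define use classes from attendance in a fixed window after first attendance, for example the first 6 months: visits per month, hours per month and any gap. Start outcome follow-up when the window closes, among pairs still at home and alive, with controls aligned to the same time origin. Alternatively, model attendance as a time-varying exposure.
2. Time the overall attendee comparison from the matched index date or first-attendance date, or treat attendance as time-varying, rather than counting from the first RAI-HC.

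Whole-trajectory classes may stay in objectives 1 and 2, with a note that total days can depend on length of follow-up.

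Cost: revised wording and some reprogramming. The registries already hold start and stop dates, attendance days and visit duration. Pairs in which someone exits before the landmark leave the class analysis, and its results then apply to people who remain at home and alive through the window.

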#### Study Outcomes

The data sources noted above enable us to examine a range of important study outcomes. Data on the time between a person’s first RAI-HC assessment and admission to a care home will come from provincial continuing care registries. Symptoms of depression will be assessed using the validated RAI-HC Depression Rating Scale [72], with scores ranging from 0 to 14 and a cut point of 3 or higher representing clinically meaningful depressive symptoms [72,73]. We will capture physical and cognitive decline, using validated RAI-HC scales [64]: the Activities of Daily Living Hierarchy (ADLh) Scale [74] and the Cognitive Performance Scale (CPS) [75]. Both scales range from 0 (no impairment) to 6 (maximum impairment), and our outcomes will be dichotomous, indicating any increase (vs no change or a decrease) between the previous and follow-up measurement in each of these scales. Using care practitioner claims data, we will generate rates of different types of primary and specialist care use (eg, family physician, specialists, nursing practitioner, and allied health providers). We will use the DAD and NACRS databases to generate rates of emergency department registrations, hospital admissions, and days in hospital (including alternative level of care) [43]. Rates will be stratified by day program use or nonuse pattern.

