Using GEEs and a similar approach as for the time-to-event models (including separate models in each province and statistical pooling of their effects), we will assess whether the other study outcomes differ by day program use or nonuse pattern. Models will include each study outcome of interest as a dependent variable, day program use or nonuse class and time of assessment as independent variables, and similar covariates (using the same stepwise approach) as the time-to-event models. Models will also include a random term to account for repeated measures within individuals. The choice of a link function will be informed by the nature of the variable and theoretical and empirical considerations. For example, the number of hospital, emergency department, or physician visits has been shown to follow a zero-inflated negative binomial distribution, sometimes requiring an offset for the natural logarithm of person-time [92]. For continuous outcomes (eg, days spent in hospitals), we will use an identity link function, and for dichotomous outcomes (eg, presence or absence of depressive symptoms), we will use a logit link function. All models will apply multiple imputation in case of missing data, which we expect to be small based on our previous work with the administrative health care data sources used in this study.

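### Long hospital stays can set the attendance-gap indicator behind the use classes, and hospital days are then compared across those classes

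*Protocol article*

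**What the plan says.** Under Exposure, the protocol article takes use patterns from the provincial continuing care registries: start and stop dates, days attended and visit duration. Three of the LCA indicators are continuous variables cut at quartiles, among them the "total number of days a person attended a day program". The fourth is a categorical variable "indicating whether a person consistently attended a day program or whether there were longer periods (several weeks) of nonattendance". Objective 1 fits the classes "using the 4 variables described in the exposures section", and the Introduction lists "ongoing versus interrupted attendance" among the patterns of interest. Nonuse is judged over the whole care trajectory: "Nonuse will be defined as no day program exposure at any time during a person" and onward through that trajectory.

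Under Study Outcomes, the hospital and emergency databases will be used to "generate rates of emergency department registrations, hospital admissions, and days in hospital (including alternative level of care", and the section adds: "Rates will be stratified by day program use or nonuse pattern". Under Objective 3, the generalized estimating equation (GEE) section states that "we will assess whether the other study outcomes differ by day program use or nonuse pattern". The models carry use or nonuse class as the exposure term, and only the adjustment variables are described as time-varying. Matching covariates are taken at the index date. Data Sources links inpatient records, with length of stay, for every cohort member.

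**The concern.** Time in hospital is time when a person cannot attend. A stay of several weeks therefore does two things: it adds to the outcome, and it can switch the gap indicator from consistent to interrupted. It also takes something off the total days attended. Nonusers are not sorted in this way, and their long stays remain in one group. Matching at the index date cannot correct a label that later hospital stays help to set.

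At stake are the class-level comparisons of hospital days. They could suggest that steady attendance protects against hospital use and that interrupted attendance raises it, even if programs do nothing. A large cohort would make that result more precise without making it less biased.

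**Working it through.** **The plan's own figures.** The plan gives no figure on this point. Its one computed figure, 1,327 participants, concerns care home admission and does not enter here. All hospital and gap rates below are assumptions.

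**Step 1: direction, using the gap indicator alone.** Assume no program effect, 4 hospital days per year from short stays, a yearly probability *p* of one long stay averaging 35 days that creates a gap, and an unrelated gap in 20% of attendees. Then:

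- consistent mean = 4
- interrupted mean = 4 + 35*p* / [1 − (1 − *p*)(0.8)]
- nonuse mean = 4 + 35*p*

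At *p* = 0.05 the bracket is 1 − 0.95 × 0.8 = 0.24. The interrupted mean is 4 + 1.75/0.24 = 11.3 and the nonuse mean is 5.75. The ratios to nonuse are 4/5.75 = 0.70 and 11.3/5.75 = 1.96. At *p* = 0.03 they are 0.79 and 1.72; at *p* = 0.10, 0.53 and 2.2. Attendees as a whole average 0.76 × 4 + 0.24 × 11.29 = 5.75, the same as nonusers, so the days are only redistributed between groups.

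A 3-year simulation under the null (200,000 attendees and 200,000 nonattendees) varied the gap threshold (21, 28 or 42 days), the stay rate (0.3 or 0.6 per year), the mean stay (8 or 14 days) and equal or unequal personal risk, giving 24 scenarios. A stay plus 7 days that reached the threshold counted as a gap. On the raw indicator, the ratios to nonattendees were 0.19-0.79 (consistent) and 1.64-2.41 (interrupted). All attendees together were at 0.99-1.01.

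**Step 2: size, using a four-indicator LCA.** The protocol's classes are not the raw indicator. A second null simulation (30,000 attendees, 0.5 stays per year, mean stay 10 days, unequal risk, 28-day gap, 20% other gaps) was therefore passed through a four-indicator LCA. Classes are ordered by their gap probability:

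| Classes | Gap probability | Share of attendees | Hospital days, ratio to nonattendees |
|---|---|---|---|
| 2 | 0.20 / 0.52 | 0.53 / 0.47 | 0.85 / 1.14 |
| 3 | 0.16 / 0.32 / 0.63 | 0.26 / 0.48 / 0.26 | 0.80 / 0.95 / 1.24 |
| 4 | 0.15 / 0.26 / 0.42 / 0.67 | 0.20 / 0.35 / 0.27 / 0.18 | 0.77 / 0.89 / 1.06 / 1.30 |

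Check for two classes: 0.53 × 0.85 + 0.47 × 1.14 = 0.99, which matches the overall attendee ratio of 0.99. The distortion is smaller than on the raw indicator but remains, and it follows the gap probability.

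**Step 3: does the repair work?** When hospital time is not counted as nonattendance, the ratios return to 0.98-1.01 on the raw indicator and 0.97-1.00 in every LCA class.

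**Step 4: would time-ordering alone suffice?** Classing on year 1 and counting hospital days in years 2-3, on the raw indicator, gives about 1.0 when risk is equal. With unequal risk it leaves 0.84-0.99 (consistent) and 1.10-1.55 (interrupted), because people with a long stay in year 1 are also at higher risk later.

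**The case against.** The strongest reply has four parts.

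- **The gap does not define a class.** It is one of four indicators, and the final number of classes is to be chosen on fit, theory and consistency across provinces. Whether any class will separate mainly on interruption is unknown. This stands. A reader might infer from Step 1 that consistent attenders will show about 30% fewer hospital days and interrupted attenders about twice as many. The documents do not support that, because those figures skip the LCA.
- **The article is condensed.** It states neither a gap threshold nor how absence is counted, and netting out inpatient days could sit in a fuller document. This stands in part: nothing says that hospital gaps must be counted. But the stated source is registry attendance data over the whole trajectory, and following that construction as written produces the bias.
- **Objective 3 is framed as attendees versus matched nonattendees, with class as a possible effect modifier.** Yearly comparisons of those two groups are also planned. This stands, and the contrast is not biased by this route, so a reader should not extend the point to it. However, those comparisons are bivariate tests, while the models use class as the exposure term.
- **An absence through illness is a real interruption of service.** This is fair for Objective 1, which describes use. It does not justify using the same label as the exposure for hospital days.

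The calculations cover hospital days only. Nothing here establishes the size for admission counts or emergency visits.

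**Conclusion.** The point holds for class-level comparisons of hospital days. The gap indicator, and to a lesser extent total days attended, can be set by long hospital stays during the follow-up in which those days are counted, so the outcome partly determines the exposure class. The direction follows from the construction: under no effect, classes with more consistent attendance look better than nonuse and classes with more interruption look worse.

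The size is uncertain. Under the assumed rates the most consistent class was at 0.77-0.85 and the most interrupted at 1.14-1.30 relative to nonusers, depending on the number of classes. Only stays long enough to produce a gap of several weeks act through the gap indicator.

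**What to change.** - **Gap indicator.** Using the linked inpatient admission and discharge dates, do not count hospital days as nonattendance when deriving it.
- **Total days attended.** Express it relative to days out of hospital.
- **Hospital outcomes.** Report the modelled any-attendance versus nonattendance contrast as the main estimate, and label class-level hospital contrasts as exploratory. That label remains advisable after the repair: the simulated non-hospital gaps were unrelated to hospital risk, and illness absences at home may not be.
- **Objective 1.** It may still describe all interruptions, with hospital-related gaps shown separately.

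The cost is one extra data step on records already linked, plus a few sentences of protocol text. Some attendees will move from interrupted to consistent.
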